### Outcome measures

#### Primary outcome

The primary outcome is Gastrointestinal-2, which is a composite outcome of time to first defecation and time to tolerance of a solid diet (22).

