### Randomization and blinding

This study has a single-blind design. Patients will be unaware of their group allocation, which will only be known to the lead investigator and acupuncture physician. The randomization sequence and allocation ratio (1:1:1:1:1:1) will be generated using the statistical software SPSS 26.0. Group allocation will be concealed using opaque envelopes, which will be distributed sequentially after patient enrolment.

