### Intervention

Each group will receive an Enhanced Recovery After Surgery (ERAS)-standardized perioperative management (20). The acupoints used in the treatment group are referenced from the China National Standard Nomenclature and Location of Meridian Points (GB 12346-2021) (21). The selected acupoints and their locations are shown in Figures 2–4. The Hwato SDZ-V (Suzhou Medical Supplies Factory) EA apparatus will be used, and the current intensity will be adjusted to the tolerance level of the patient. Each treatment will last for 30 min and the initial session will commence on the first postoperative day. Treatment sessions will be provided once daily in the morning until the patient regains spontaneous flatus and can tolerate oral intake of solid food. All acupuncture maneuvers will be performed independently by the same acupuncturist, who has at least 5 years of work experience. The acupuncturist will not be replaced at any point during the study.

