#### Control group

Only ERAS-standardized perioperative management, without TEAS or EA, will be performed in the control group.

All acupoints will be routinely disinfected. The acupoints in the distal limb will be punctured straight through the skin to a depth of 25–30 mm using disposable stainless steel needles (0.25 × 40 mm, Suzhou Jiajian, Jiangsu, China). The needle will then be twisted slightly to achieve the de qi sensation, and the EA apparatus will be connected with a set of electrodes in the ipsilateral Neiguan (PC6), Hegu (LI4), Zusanli (ST36), and Xiajuxu (ST39). The abdominal acupoints will be stimulated with a self-adhesive electrode sheet with electrical conductivity, and the ipsilateral Liangmen (ST21) will be connected with a set of electrodes at Daheng (SP15).

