#### Secondary outcomes

Secondary outcomes comprise the following: (1) time of first spontaneous exhaustion after operation; (2) time of first spontaneous defecation after operation; (3) time of first tolerance to oral intake of solid food after operation; (4) time to first ambulation after surgery; (5) VAS scores for postoperative daily pain and nausea and vomiting; (6) postoperative daily incidence of nausea and vomiting; (7) length of hospital stay, from surgery to discharge; (8) incidence of postoperative complications; and (9) acceptability of acupuncture therapy on a 5-point Likert scale (very acceptable, moderately acceptable, somewhat acceptable, moderately unacceptable, and totally unacceptable).

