### Limitation

This trial will not include a sham control arm, and a placebo response and effect analysis is lacking. Nevertheless, some studies on the use of acupuncture for gastrointestinal symptoms have shown that EA may have more significant benefits than sham acupuncture, despite a placebo effect (36, 37).

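### The article claims masking that its untreated, no-sham control rules out, and one of the two GI-2 components is open to influence from people who can see the treatment

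*Protocol article*

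**What the plan says.** **Outcome.** Under Primary outcome, GI-2 is "a composite outcome of time to first defecation and time to tolerance of a solid diet". The rule for combining the two times is not given. Under Secondary outcomes both components also appear on their own: "time of first spontaneous defecation after operation" and "time of first tolerance to oral intake of solid food after operation".

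**Masking.** The design is called single-blind. Under Randomization and blinding: "Patients will be unaware of their group allocation, which will only be known to the lead investigator and acupuncture physician".

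**What the arms receive.** The Intervention section gives every arm ERAS-standardized care. Active arms also have a 30-minute session each day, starting the day after surgery: "Treatment sessions will be provided once daily in the morning until the patient regains spontaneous flatus and can tolerate oral intake of solid food". EA uses needles in the limbs, TEAS uses adhesive electrodes on the abdomen, and the combination arms use both. For controls: "Only ERAS-standardized perioperative management, without TEAS or EA, will be performed in the control group". The Limitation section adds: "This trial will not include a sham control arm".

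**The concern.** Two things meet here.

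First, the masking statement describes a property that the design does not have. Patients know whether they are being needled or wear electrodes, and so does anyone at the bedside during the morning session. Active versus control and EA versus TEAS are both visible. The waveform (2 Hz against 2/50 Hz) is the only factor that might be hidden.

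Second, time to tolerance of solid food is bounded below by the time food is given. If knowledge of treatment affects when a patient is fed, or when tolerance is judged and recorded, GI-2 can differ between arms with no difference in gut recovery. The treatment-stopping rule uses the same event. In the six active arms, an acupuncture physician who knows the allocation therefore needs each patient's solid-food status. Nothing in the article describes a matching daily check for controls.

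At stake are the active-versus-control and modality contrasts on the primary outcome. The Limitation section concedes the missing sham only as a question of placebo response. It does not address influence on how an outcome component is timed.

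**Working it through.** **1. Masking statement against the arms as described**

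| Contrast | What differs at the bedside | Can it be masked as designed? |
|---|---|---|
| Active vs control | daily session vs none, no sham | No |
| EA vs TEAS vs both | limb needles, abdominal electrodes, or both | No |
| Continuous vs dilatational wave | stimulator setting | Possibly |

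**2. The plan's figures (Sample size section)**

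- Pilot GI-2, mean ± SD in hours: cEA 84.8 ± 36.1; cTEAS 86.8 ± 40.1; cTEAS+EA 70.3 ± 39.3; dEA 78.3 ± 42.2; dTEAS 81.2 ± 44.2; dTEAS+EA 64.1 ± 36.3; control 110.8 ± 42.3.
- Planned size: 80 × 7 = 560. With 20% dropout, 80 × 0.8 = 64 evaluable per arm.
- The size is attainable from the smallest active-versus-control difference. SD² = (40.1² + 42.3²)/2 ≈ 1698.7, and n = 2(1.960 + 1.282)² × 1698.7/24.0² ≈ 62 per arm. Then 62/0.8 gives 78 per arm, or 546 in total. The test used is not named, so this shows only that 560 is attainable. Only the 64 is used below.

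Differences to compare against:
- EA vs TEAS: 86.8 − 84.8 = 2.0 h; 81.2 − 78.3 = 2.9 h
- Combination vs EA: 84.8 − 70.3 = 14.5 h; 78.3 − 64.1 = 14.2 h
- Active vs control: smallest 110.8 − 86.8 = 24.0 h; largest 110.8 − 64.1 = 46.7 h

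**3. How far a feeding difference moves GI-2**

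Assumptions, none from the documents: GI-2 is the later of the two times, there is no true difference in gut recovery, and feeding time shifts in one arm only. For normal components with means a (diet) and b (defecation), common SD s and correlation r, let θ = s√(2(1 − r)) and d = (a − b)/θ. Then

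E[GI-2] = aΦ(d) + bΦ(−d) + θφ(d).

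One case: a = b = 75 h, s = 40 h, r = 0, so θ = 56.57.
- No shift: 75 + 56.57 × 0.3989 = 97.6 h.
- Diet 24 h later: d = 0.424, so 99 × 0.664 + 75 × 0.336 + 56.57 × 0.3646 = 111.6 h.
- Shift: 14.0 h. It is smaller than 24 h because defecation is often the later event.

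Two sets of scenarios, by simulation:

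| Set | Diet is later event | 12 h shift | 24 h shift |
|---|---|---|---|
| A: lognormal, defecation mean 60–75 h (SD 38), diet 45–70 h (SD 34), r 0.3–0.5; diet earlier in one arm | 15–66% | 1.4–6.9 h | 2.2–11.8 h |
| B: SD 40 h, diet mean 75 h, defecation 75 or 95 h, r 0–0.8; diet later in control | 21–50% | 3.6–7.2 h | 9.3–16.4 h |

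**4. Chance of a spurious result (set B, 64 per arm)**

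For one unadjusted active-versus-control comparison, the chance of p < 0.05 in the direction of the bias is Φ(shift/SE − 1.96), with SE = SD√(2/64). With no shift it is 2.5%.
- 12 h: 8–20%. Top case: 6.5 h with SD 33.0 gives SE 5.83 and 20%.
- 24 h: 28–68%. Top case: 16.4 h with SD 38.3 gives SE 6.77 and 68%.

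**The case against.** **The feeding pathway is not documented.** A reader might infer that ward staff decide at their discretion when to offer solid food. The article does not say so. It mentions neither ward staff nor an offer of food, and all arms share ERAS care whose feeding rule is not shown. This stands. A strict common rule would narrow the exposure, so the mechanism is a risk and not a demonstrated bias. The masking contradiction does not depend on it.

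**Offer time may well be collected.** A reader might infer that it is not. An outcome list in a condensed article cannot show what is on the case report form. This stands, and the fix is worded accordingly.

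**The components are already reported separately.** This stands in part. A GI-2 effect confined to diet would show in the planned secondary outcomes, but the article does not say how such a pattern would be read.

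**The size is modest and the inputs are assumed.** This stands. EA and TEAS are also both active, so there is no evident reason for bedside staff to favour one of them by 12 to 24 h.

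**Offer time is measured after randomisation.** If diet is advanced on signs of recovery, a true gut effect would itself bring the offer forward. This stands. It rules out discounting any difference that offer time explains, and it rules out an analysis that starts the clock at the offer. Either could discard a real benefit.

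**Conclusion.** The masking statement is wrong as written. Active versus control and EA versus TEAS are not masked from patients or from anyone at the bedside. Because one of the two GI-2 components cannot occur before solid food is given, the primary outcome is exposed to that lack of masking. The exposure is inferred from the design. The article documents no allocation-dependent feeding.

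If GI-2 is the later of the two times, a 12 h feeding difference moves its mean by roughly 1 to 7 h and a 24 h difference by roughly 2 to 16 h. This can exceed the 2.0 and 2.9 h EA-versus-TEAS differences, and at 24 h it gives a 28–68% chance of a significant single comparison in set B with no true effect.

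Two stronger readings fail. Feeding differences of up to 24 h do not account for the pilot active-versus-control differences, the smallest of which is 24.0 h. Nor can half of the primary outcome be said to rest on feeding: diet is one of two components, and its weight is unknown without the combination rule. The point should be acted on, but it does not invalidate the trial.

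**What to change.** 1. Correct the Randomization and blinding section. State that active versus control and EA versus TEAS are not masked from patients or bedside staff, and that at most the waveform may be.
2. If it is not already on the case report form, take from the ward chart the time solid food was first permitted, in all seven arms, and report it descriptively by arm. Do not adjust for it, and do not use it to accept or reject a GI-2 difference.
3. Pre-specify that GI-2 is reported beside its two components, with time to first defecation as the supportive analysis because it is less directly tied to feeding decisions.
4. Pre-specify that a GI-2 difference seen only in the diet component is interpreted with caution, given the lack of masking.

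Cost: one chart-derived time field, no extra patients, and a supportive analysis on data already collected. The downside is a more cautious claim if the effect lies only in the diet component. No feeding rule or treatment schedule changes.

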#### Secondary outcomes

Secondary outcomes comprise the following: (1) time of first spontaneous exhaustion after operation; (2) time of first spontaneous defecation after operation; (3) time of first tolerance to oral intake of solid food after operation; (4) time to first ambulation after surgery; (5) VAS scores for postoperative daily pain and nausea and vomiting; (6) postoperative daily incidence of nausea and vomiting; (7) length of hospital stay, from surgery to discharge; (8) incidence of postoperative complications; and (9) acceptability of acupuncture therapy on a 5-point Likert scale (very acceptable, moderately acceptable, somewhat acceptable, moderately unacceptable, and totally unacceptable).

### Safety evaluation

EA-related safety evaluation during treatment includes the documentation of broken needles, fainting due to needles, intolerable pinprick pain, local hematoma, infection, abscess, and other incidences of discomfort after pinprick. Adverse events will be recorded by the acupuncture physician in a standardized form.

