Therefore, the primary purpose of this randomized controlled study is to compare the efficacy and safety of three acupoint stimulation methods and two EA instrument waveforms in facilitating rapid recovery after abdominal surgery, with the overarching aim of informing the development of an objective and unified standard for acupuncture use to facilitate rapid postoperative recovery.

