## Methods and analysis

### Study design

This is a prospective, single-center, parallel, single-blind, randomized controlled trial. Effectiveness and safety will be compared among three acupoint stimulation methods (EA, TEAS, TEAS+EA) and two EA instrument waveforms (continuous waves, dilatational waves) to determine their suitability for promoting them in postoperative rehabilitation. This study will be conducted in accordance with the principles of the Declaration of Helsinki. The “Standard Protocol Items: Recommendations for Interventional Trials” checklist is provided in Supplementary Material 1.

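### Safety is to be compared between EA and TEAS, but the safety section is written around needling and names no TEAS event, so on the listed items that contrast is asymmetric in favour of TEAS-only

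*Protocol article*

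**What the plan says.** Safety is part of the declared comparison. The protocol article states under Study design: "Effectiveness and safety will be compared among three acupoint stimulation methods (EA, TEAS, TEAS+EA) and two EA instrument waveforms". The Introduction makes it part of the primary purpose, which is to "compare the efficacy and safety of three acupoint stimulation methods and two EA instrument waveforms in facilitating rapid recovery after abdominal surgery". Neither sentence names the control group.

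The Safety evaluation section has two sentences. The first is limited to EA and to the treatment period: "EA-related safety evaluation during treatment includes the documentation of broken needles, fainting due to needles, intolerable pinprick pain", continuing with "local hematoma, infection, abscess, and other incidences of discomfort after pinprick". The second is general: "Adverse events will be recorded by the acupuncture physician in a standardized form".

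Four further statements bear on this:

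- Randomization and blinding says of the allocation, "which will only be known to the lead investigator and acupuncture physician".
- Intervention says: "All acupuncture maneuvers will be performed independently by the same acupuncturist".
- The intervention descriptions give the cTEAS and dTEAS arms abdominal surface electrodes and no needles. For control they say: "Only ERAS-standardized perioperative management, without TEAS or EA, will be performed in the control group".
- Secondary outcomes include the incidence of postoperative complications, daily pain and nausea/vomiting scores, and daily nausea/vomiting incidence, none of them restricted by arm.

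**The concern.** A safety comparison between two modalities needs the same questions asked of both, over the same period. Here the named events belong mainly to one modality. A patient treated only through surface electrodes cannot have a broken needle, needle fainting or pinprick pain. Even the closing catch-all item refers to discomfort after a needle prick. The harms that surface stimulation could plausibly cause, such as a skin reaction under the electrode or discomfort from the current, are not named, although Intervention sets the current at the patient's tolerance level.

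The recorder knows the allocation and appears to be the person giving the treatment, so the reporting of subjective events is not protected by blinding.

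At stake is the reading of the EA-versus-TEAS safety result. A lower count in the TEAS-only arms would mix a true absence of needle injury with the absence of any matching question about electrode harm. This is not a detail that an analysis plan can repair, because events that were never asked about cannot be recovered at analysis.

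**Working it through.** The plan gives no safety event rate and no figure for this point, so there is nothing to reproduce. The check is a reading of the sections against each other, followed by an illustration.

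**1. Arms by exposure** (80 per group, from Sample size)

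- Needled: cEA, cTEAS+EA, dEA, dTEAS+EA, 4 × 80 = 320.
- Not needled: cTEAS, dTEAS, control, 3 × 80 = 240.
- EA-only (cEA + dEA): 2 × 80 = 160. TEAS-only (cTEAS + dTEAS): 2 × 80 = 160.

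**2. Listed items against exposure**

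| Listed item | Possible without a needle? |
|---|---|
| Broken needle | No |
| Fainting due to needles | No |
| Intolerable pinprick pain | No |
| Other discomfort after pinprick | No, by its wording |
| Local hematoma, infection, abscess | Yes by wording, but listed under an EA-related heading |
| Electrode-site reaction, surface-stimulation discomfort | Not listed |

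**3. Window and recorder**

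- The evaluation runs during treatment. TEAS-only patients have daily sessions and so have a window. Control patients have no session and so have no defined window.
- In the active arms treatment ends when bowel function and solid intake return, so the length of observation depends on recovery, which the trial expects to differ by arm.
- The recorder is the acupuncture physician, who is unblinded. That this is the single treating acupuncturist is a strong inference. The article does not say so outright.

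**4. Which contrasts are affected**

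- EA-only versus TEAS-only: affected, in favour of TEAS-only.
- cEA v dEA, cTEAS v dTEAS, cTEAS+EA v dTEAS+EA: not distorted by the list, since both sides have the same exposure.
- Active arms versus control: not a stated safety comparison. It arises only if the among-groups chi-square or Fisher test in Statistical analysis is applied to adverse events in all seven arms.

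**5. Illustration for the stated contrast**

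Assumptions, none from the documents: a discomfort event has the same true rate q in every arm; it is captured in every needled patient and in no TEAS-only patient; nobody drops out. Let X be the recorded count in the EA-only arms, X ~ Binomial(160, q), against 0/160.

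Two-sided Fisher: 5/160 v 0/160 gives p = 0.061; 6/160 v 0/160 gives p = 0.030. So p < 0.05 needs X ≥ 6.

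| True rate q | Expected X = 160q | P(X ≥ 6) |
|---|---|---|
| 2% | 3.2 | 10% |
| 3% | 4.8 | 35% |
| 5% | 8.0 | 82% |

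Under these assumptions there is no true difference, so every such result would be spurious. Zero capture is the worst case. Partial capture shrinks the figures but does not change the direction.

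**The case against.** The strongest reply is that the section is open-ended. The list is introduced as inclusive, the sentence on recording adverse events is not limited to EA arms, and the standardized form is not shown. A journal article commonly leaves the content of a form to the full protocol. Hematoma and infection are not needle-only by wording. TEAS-only patients are treated daily, apparently by the recorder, so they can report events. Postoperative complications, pain and nausea/vomiting are collected without restriction by arm. And fewer needle injuries where no needle is used is a true difference in risk.

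Most of this stands and limits the point. It does not remove it: what the article does fix is an EA-specific scope, mainly needle items and an unblinded recorder, beside a declared EA-versus-TEAS safety comparison. The postoperative complication outcome covers surgical morbidity and need not capture a skin reaction under an electrode.

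Four stronger readings are tempting and are not supported:

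- A reader might infer that control also looks safer by construction. The stated safety comparison never names control, and the article does not say that the acupuncture physician does not see control patients. Only the undefined window stands, and only if all groups are tested.
- A reader might infer that all safety data are biased. The asymmetry is shown for the listed items only.
- A reader might pool 320 needled against 240 non-needled patients and, at an assumed 5% rate, find significance in over 99% of trials. That pooling is planned nowhere, assumes zero capture in all 240, and is sensitive to the rate: the same calculation gives 62% at 2%.
- A reader might infer that the form would confirm the Discussion's statement that TEAS is safer than EA. That statement concerns abdominal acupoints, which no arm needles, so this trial cannot test it.

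**Conclusion.** The point holds in a limited form. For the listed items, the EA-only versus TEAS-only safety contrast (160 v 160) is asymmetric and favours TEAS-only, whatever the rate of TEAS-related harm. The asymmetry comes from an EA-specific list with no TEAS counterpart. An unblinded recorder, who appears also to be the treater, adds to it. The direction follows from the text. The size does not: the 10%, 35% and 82% figures rest on assumed rates of 2%, 3% and 5%, equal true risk and complete non-capture without needles. Waveform comparisons within a modality are not affected, and neither efficacy nor the sample size is touched. The change should be made because the safety comparison is a declared aim and the remedy is cheap.

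**What to change.** Revise the Safety evaluation section as follows:

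- Use one adverse-event form with the same items in all seven arms, over one stated postoperative window that does not depend on treatment sessions, for example first postoperative day to discharge.
- Add electrode-site skin reactions and stimulation discomfort to the listed events.
- Compare all-cause adverse events across arms. Report needle-specific events descriptively, within the four needled arms only.
- If staff who do not give the treatment already collect the daily outcomes, have them complete the form. The article does not say who collects those outcomes, so if there are no such staff, keep the present recorder and state the lack of blinding as a limitation.

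The cost is a revised form, a few changed sentences, and slightly more recording in the TEAS-only and control arms. A separate assessor might need extra staff and is not required.

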### Sample size

The determination of the sample size was based on the following pre-experimental results for the primary outcome measure, Gastrointestinal-2: cEA, 84.8 ± 36.1 h; cTEAS, 86.8 ± 40.1 h; cTEAS+EA, 70.3 ± 39.3 h; dEA, 78.3 ± 42.2 h; dTEAS, 81.2 ± 44.2 h; dTEAS+EA, 64.1 ± 36.3 h; and control, 110.8 ± 42.3 h. PASS 15 software was used to determine the sample size of 560 patients (80 patients in each group; α = 0.05 [two-sided], β = 0.1 [90% power], with an assumed 20% dropout rate).

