### Statistical analysis

The data will be analyzed using SPSS 26.0. All statistical tests will be two-sided, and a *p*-value of less than 0.05 will be considered statistically significant. Measurement data conforming to a normal distribution will be expressed as mean ± standard deviation (x ± s). Comparisons among groups will be performed *via* one-way analysis of variance, using the Student–Newman–Keuls q-test for pairwise comparisons. Variables that do not follow a normal distribution will be analyzed with the Kruskal–Wallis H-test. Categorical and count data will be described as frequency or percentage and compared among groups using the chi-square or Fisher's test.

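### The unqualified 90% power fits active-versus-control comparisons; the modality and waveform contrasts named as the primary purpose have far less, about 12–15% for waveform and 6–7% for EA versus TEAS.

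*Protocol article*

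**What the plan says.** The Sample size section of the protocol article bases the calculation on pilot means and SDs of Gastrointestinal-2, the primary outcome. The three continuous-wave arms are listed as "cEA, 84.8 ± 36.1 h; cTEAS, 86.8 ± 40.1 h; cTEAS+EA, 70.3 ± 39.3 h". The three arms with the other waveform follow as "dEA, 78.3 ± 42.2 h; dTEAS, 81.2 ± 44.2 h; dTEAS+EA, 64.1 ± 36.3 h". The list ends with the untreated comparison arm: "control, 110.8 ± 42.3 h". The section then reports that "PASS 15 software was used to determine the sample size of 560 patients". The settings behind that number are given as "80 patients in each group; α = 0.05 [two-sided], β = 0.1 [90% power], with an assumed 20% dropout rate". The 90% is attached to no particular comparison.

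The Introduction closes by stating that "the primary purpose of this randomized controlled study is to compare the efficacy and safety of three acupoint stimulation methods and two EA instrument waveforms". Study design and the Discussion repeat that aim.

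The Statistical analysis section plans a one-way analysis of variance over the groups, "using the Student–Newman–Keuls q-test for pairwise comparisons" (SNK below). It describes no factorial or pooled analysis of the six active arms.

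**The concern.** A reader who meets one power figure and one declared primary purpose will join the two and take the trial to have 90% power to separate modalities and waveforms. The pilot means suggest otherwise. Each active arm differs from control by 24 to 47 h, but the two waveforms differ by about 6 h within a modality, and EA differs from TEAS by 2 to 3 h within a waveform. A size that suits the first set of differences cannot suit the others when the SDs are all near 40 h.

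The interpretation of the result is at stake. The article says its results will inform a unified standard for acupuncture after surgery, and it presents the waveform comparison as new. If the true waveform difference is about what the pilot showed, each within-modality comparison will miss it roughly 85–88% of the time even before multiplicity is considered. Without a warning in the plan, such a null result is easy to over-interpret.

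**Working it through.** **Inputs** (all from Sample size): the seven means and SDs above; two-sided α = 0.05; 80 randomised per arm; 20% dropout, so 80 × 0.8 = 64 evaluable per arm.

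**Formula for a pair.** s = √((s₁² + s₂²)/2); SE = s√(2/64); δ = difference/SE. Power is the probability that a noncentral t with 126 df and noncentrality δ falls outside ±1.979.

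**Reproducing the stated size.** The smallest active-versus-control difference is cTEAS: 110.8 − 86.8 = 24.0 h, with s = √((40.1² + 42.3²)/2) = 41.2. By the t-test, 90% power needs 63 evaluable per arm. 63/0.8 = 78.75, so 79 per arm, or 553 in total, against the stated 80 and 560. At 64 evaluable, SE = 41.2 × √(2/64) = 7.29, δ = 3.29 and power is 90.5%. The stated figures are therefore consistent with this contrast.

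The F-tests do not lead to 80. The seven-arm F-test (pooled SD 40.2, SD of the means 13.8, f = 0.343) needs 23 evaluable per arm, or 29 after dropout. An F-test over the six active arms needs about 70, or 88 after dropout.

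**Power at 64 evaluable per arm.** The SNK column is simulated with normal data and the article's means and SDs.

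| Contrast | Difference (h) | s (h) | δ | Unadjusted | SNK |
|---|---|---|---|---|---|
| cTEAS vs control | 24.0 | 41.2 | 3.29 | 90.5% | 89% |
| cEA vs control | 26.0 | 39.3 | 3.74 | 96.0% | 93% |
| dTEAS vs control | 29.6 | 43.3 | 3.87 | 97.0% | 96% |
| dEA vs control | 32.5 | 42.3 | 4.35 | 99.1% | 98% |
| either combination vs control | 40.5, 46.7 | 40.8, 39.4 | 5.61, 6.70 | >99.9% | >99% |
| *Waveform:* cEA vs dEA | 6.5 | 39.3 | 0.94 | 15.3% | 5% |
| cTEAS vs dTEAS | 5.6 | 42.2 | 0.75 | 11.6% | 5% |
| cTEAS+EA vs dTEAS+EA | 6.2 | 37.8 | 0.93 | 15.1% | 8% |
| *EA vs TEAS:* continuous | 2.0 | 38.2 | 0.30 | 6.0% | 2% |
| dilatational | 2.9 | 43.2 | 0.38 | 6.6% | 2–3% |
| *Combination vs single:* dEA | 14.2 | 39.4 | 2.04 | 52.6% | 30% |
| cEA | 14.5 | 37.7 | 2.17 | 57.8% | 26% |
| cTEAS | 16.5 | 39.7 | 2.35 | 64.5% | 36% |
| dTEAS | 17.1 | 40.4 | 2.39 | 66.0% | 43% |

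With no dropout at all (80 evaluable), the three unadjusted ranges become 13–18%, 6–7% and 62–76%.

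**The same result in hours.** With SD 40.2 and 64 per arm, the difference detectable with 90% power is (1.960 + 1.282) × 40.2 × √(2/64) ≈ 23 h. The single-factor differences run from 2.0 to 17.1 h.

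**Evaluable patients per arm for 90% (unadjusted t).** Waveform 768–1,195; EA vs TEAS about 4,670–7,650; combination vs single 119–163.

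**If the six active arms were pooled as a 3×2 layout** (64 per cell, common SD 39.8, unadjusted):
- Waveform means are 80.6 and 74.5 h, a difference of 6.1 h with 192 per side: 32%.
- Modality means are EA 81.55, TEAS 84.0 and combination 67.2 h, with 128 per side. Combination vs EA (14.35 h) 82%; combination vs TEAS (16.8 h) 92%; EA vs TEAS (2.45 h) about 8%.
- Three-level modality F-test: 91%.

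**The case against.** It is tempting to say that the 90% holds only against control. That is too strong. The planned seven-arm F-test has more than 99.9% power. An F-test over the six active arms would have 87.5%, and a pooled three-level modality test about 91%. Two active pairs also reach about 90% unadjusted: cTEAS vs dTEAS+EA (91.5%) and cEA vs dTEAS+EA (89.4%).

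These facts stand, but they do not rescue the stated purpose. The seven-arm result is driven by the control arm and does not say which modality or waveform is better. The six-arm and pooled tests are not in the Statistical analysis section. The two strong pairs change modality and waveform together, so they isolate neither, and they fall to about 70% and 60% under SNK.

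A reader might also infer that the sample size was miscalculated. It was not: 80 per arm reproduces to within one patient. That the software was run on cTEAS versus control is an inference from the arithmetic; the article does not say so. Nor is it a fault that a condensed article leaves out the software settings. The point is the mismatch between an unqualified power figure and the declared purpose, and both are printed.

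Finally, nothing in the article says that a non-significant waveform result will be taken as equivalence, or that 6 h is the difference worth detecting. The first is a risk to guard against, not a stated intention. On the second, the pilot means are the only effect sizes the article offers, and it offers them as the basis for the size.

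**Conclusion.** The concern holds as a mismatch between power and objective. With 64 evaluable per arm, the design gives about 90% or more for each active arm against control, unadjusted, and about 89% under SNK for the weakest. For the contrasts that isolate one element of the primary purpose, it gives 12–15% (waveform), 6–7% (EA vs TEAS) and 53–66% (combination vs single) unadjusted. Under the planned SNK test these become about 5–8%, 2–3% and 26–43%. Pooling would make the combination-versus-single question reasonably powered, but not waveform or EA vs TEAS.

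The documents do not support the wider conclusion that the trial cannot address modality at all. The clear shortfall is in waveform and EA vs TEAS, with a moderate one for combination vs single in separate pairs.

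The figures assume that the pilot means and SDs are the true values (the article gives no pilot sample sizes), that dropout is 20% in every arm, and that the data are roughly normal, which is the condition under which the plan uses ANOVA with SNK.

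**What to change.** Keep N = 560.

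1. In Sample size, restate the claim as about 90% power, for unadjusted pairwise tests, for each active arm versus control. Beside it, give the power of the waveform, EA-vs-TEAS and combination-vs-single contrasts under the planned test.
2. State that waveform and EA-vs-TEAS results will be reported as estimated differences with confidence intervals, and that a non-significant result will not be read as equivalence. Align the statements of purpose in the Introduction, Study design and Discussion with this.
3. Quote the pooled figures (82% combination vs EA, 92% combination vs TEAS, 32% waveform, about 8% EA vs TEAS, all unadjusted) only if the Statistical analysis section is also amended to add a 3×2 factorial analysis of the six active arms. Otherwise they would describe an analysis that the plan does not contain.

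The cost is a less favourable stated power, matching edits to the aims, and a little more analysis work if the factorial model is added. No extra patients are needed.
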